## Abstract

**Methodology::**

This trial is designed as a pragmatic double-center, single-blind, and 3-arm (1:1:1 ratio) randomized controlled trial. The recruited patients with LDH will be randomly allocated to the intervention (traction weight is 40% or 60% of its body weight) or control (traction weight is 20% of its body weight) group. Traction will be completed within 6 consecutive weeks (3 times a week), with 10 minutes of traction for the first 3 weeks, 20 minutes of traction for the next 3 weeks. After the experiment is completed, we will establish an experiment-related database. The software of SPSS, version 21 (SPSS Inc. Chicago, IL) will be used for statistical analysis, and measurement data will be expressed via mean and standard deviation (mean ± SD).

**Discussion::**

Once the trial is completed, we will publish the study in journals in both Chinese and English to promote the dissemination and use of the results. In addition, we also plan to promote the research results at various academic conferences both domestically and internationally.

## 1. Introduction

Low back pain (LBP) is 1 of the most common presenting complaints in the world, and about 70% to 80% of the population sustains an episode once in their lifetime.^[1,2]^ Upright walking human beings need to stand and sit for a long time, thus their lumbar vertebrae bear greater load that might lead to intervertebral disc degeneration and disorder of relevant motion segment structures, such as small joints, ligaments, and muscles. Consequently, the lumbar spine loses its mechanics balance and eventually leading to LBP.^[3,4]^

However, LBP is a clinical symptom rather than a specific diagnosis. LBP is the most common clinical manifestation of lumbar disc herniation (LDH). LDH represents a frequent disorder encountered in current clinical practice and is associated with significant disability and morbidity.^[5]^

Currently, non-operative treatment is the first-line treatment for most LDH patients.^[6,7]^ Complementary and alternative treatments are the main focus,^[8]^ such as physical therapy/exercises,^[9]^ spinal manipulation,^[10]^ traction (manual or mechanical),^[11]^ transcutaneous electrical stimulation,^[12]^ acupuncture,^[13]^ herbal supplementation, et cetera.^[14]^ Traction is the most popular treatment for LDH among all listed. Traction is a broad term that includes mechanical traction, automatic traction, manual traction, gravity traction, and water traction, et cetera.^[15–18]^ And, these traction treatment method varies in their traction force, traction frequency, treatment time, and duration of treatment. Apart from this, the therapeutic effectiveness of traction is not been recognized by everyone. For example, some studies believe that traction is not an effective treatment method for all LDH patients.^[19,20]^ Therefore, it is very necessary to develop a large-scale and more standardized randomized controlled trial (RCT) to evaluate the therapeutic effectiveness of traction on treating LDH patients.

Continuous and controllable lumbar traction can: reduce the pressure in the intervertebral disc; alleviate the pressure of the lumbar facet joints to correct the disorder of the facet joints, and balance the various muscle groups of the lumbar spine to achieve its effective biomechanics effects. Self-gravitation traction is 1 of them.^[21]^ Thus, our team has developed a self-gravitation traction device to achieve continuous and controllable lumbar traction. The aim of this RCT is to evaluate the effectiveness and safety of the self-gravitation traction device on treating LDH and to confirm the positive effect of the device on the treatment of LDH.

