### 2.1. Trial design

This trial is designed as a pragmatic double-center, single-blind, and 3-arm (1:1:1 ratio) RCT to evaluate the effects of self-gravitation traction on LDH patients. The trial is being conducted in 2 hospitals in Lanzhou, China (Affiliated Hospital of Gansu University of Chinese Medicine and Gansu Provincial Hospital of Traditional Chinese Medicine). The recruited LDH patients are randomly allocated into the intervention group (traction load is 40% or 60% of their body weight) or control group (Traction weight is 20% of its body weight).^[18,20,22]^ Traction treatment procedure is completed within 6 consecutive weeks (3 times a week), 10 minutes’ traction for the first 3 weeks, then increase to 20 minutes for the next 3 weeks. See details in Figure 1.

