#### 2.4.2.
*Phystrac mechanical traction therapy*.

Participants are in a supine position on the traction machine through adjustment, with hip and knee joints flexed at 90°, and double-fixed with a pelvic belt and ankle joint U-shaped feet (Fig. 3A). Start the weighing sensor system, apply mechanical load in advance through the axial pulling of the armpit on the horizontal plane, and will use the load cell to measure the mechanical traction. It is initially set as the preload, and on this basis, the shaft is gradually rotated to the head-down and the foot-high position, and the bodyweight will be used to complete the equivalent transformation of force (Fig. 3B). When the traction device rotates to a certain angle (the angle measuring instrument records the traction angle), the preload of the horizontal mechanical load will completely transform into its gravity. Controlled and quantified traction, continuous and repeated self-weight traction at this tilt angle.

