## 3. Discussion

As a high incidence disease, intervertebral disc herniation is a spinal condition that can cause back pain and/or radiculopathy.^[27]^ Traction is an effective treatment, but it is not standardized at present. Therefore, it is very important to formulate the optimal traction dose and traction parameters. The self-gravitation traction device independently developed by our team completely converts the preload loaded by horizontal machinery into its gravity control and quantified traction force through the equal conversion of force, to complete the accurate control and quantification of traction force. It can carry out continuous traction for a certain time to make up for the defects of individual differences and poor tissue compliance during continuous mechanical traction, to provide a reliable and accurate research method for lumbar traction in the treatment of LDH.

After the completion of this RCT, we will publish the study in journals in both Chinese and English to promote the dissemination and use of the results. In addition, we also plan to promote the research results at various academic conferences both domestically and internationally.

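### The stated aim is to confirm that the device works, but the arms appear to differ only in traction load, so the trial compares loads and does not test the device against its absence

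*Protocol article*

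**What the plan says.** **Aim.** The Introduction (section 1) notes that the value of traction is disputed and calls for a trial "to evaluate the therapeutic effectiveness of traction on treating LDH patients". It then gives the aim of this trial: to "evaluate the effectiveness and safety of the self-gravitation traction device on treating LDH and to confirm the positive effect of the device". Section 2.1 describes a "pragmatic double-center, single-blind, and 3-arm (1:1:1 ratio) RCT to evaluate the effects of self-gravitation traction on LDH patients".

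**Arms.** Section 2.1 allocates patients to the "intervention group (traction load is 40% or 60% of their body weight" or to the "control group (Traction weight is 20% of its body weight". Citations follow that sentence, but the article gives no reason of its own for 20%.

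**Delivery.** Section 2.1 gives one schedule without distinction by arm: "Traction treatment procedure is completed within 6 consecutive weeks (3 times a week", with the same session lengths for everyone. Section 2.4.2 describes one procedure for participants in general: "Participants are in a supine position on the traction machine through adjustment". A horizontal preload is applied and the table is then tilted head-down until gravity has taken over that preload.

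**Comparison.** Section 2.5.2 makes change in VAS pain from baseline, compared between the groups, the primary outcome.

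**Discussion (section 3).** Here the question is put differently: "it is very important to formulate the optimal traction dose and traction parameters".

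**The concern.** Whether a device works is a question about the device against something else: no traction, a sham, usual care or another treatment. The article describes no such comparator. The control patients appear to receive the device too, at a lower load. The randomised contrasts then answer a different question, namely whether more load gives more pain relief than less load.

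The mismatch affects what may be concluded. If 20% already helps, the trial may find little or no difference although the device is useful. If all groups improve, an aim worded as confirmation invites a reader to credit that improvement to the device, although it also contains natural recovery and regression to the mean. On safety, a harm that occurs equally at every load has no untreated group against which to measure it.

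**Working it through.** **1. Can the 20% arm be anything other than device treatment?** Section 2.1 defines the control by a traction load. Section 2.4.2 gives one machine procedure and no separate one for controls. No sham or non-traction arm appears anywhere. Use of the device at 20% is not stated in one explicit sentence, but it is the only reading the text supports.

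**2. What the contrasts estimate.** Let E20, E40 and E60 be the mean VAS improvement caused by the device at each load, relative to no device. Natural recovery and regression to the mean have the same expectation in all randomised arms and drop out. The two contrasts with control are

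- 40% v 20%: E40 − E20
- 60% v 20%: E60 − E20

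The device-level aim concerns E20, E40 and E60 themselves. None of these can be recovered from the differences unless E20 is known.

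**3. Three assumed cases (mm on the VAS).**

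| E20, E40, E60 | 40% v 20% | 60% v 20% |
|---|---|---|
| 20, 20, 20 | 20 − 20 = 0 | 20 − 20 = 0 |
| 0, 0, 0 | 0 − 0 = 0 | 0 − 0 = 0 |
| 10, 15, 20 | 15 − 10 = 5 | 20 − 10 = 10 |

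The first two cases, a useful device and a useless one, give the same expected result. In the third, the contrasts show 5 and 10 mm where the device effects are 15 and 20 mm.

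**4. The plan's own sample size.** Section 2.2.2 gives 300 patients, 100 per group, based on an unpublished pilot. The article gives no effect size, SD or power, so the figure cannot be reproduced.

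**5. What 100 per arm can detect (context only).** Inputs from the article: n = 100 per arm (section 2.2.2) and two-sided alpha 0.05 (section 2.6). Assumed: 80% power and an SD of 20 to 30 mm.

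- Standardised difference: (1.96 + 0.8416) × √(2/100) = 2.8016 × 0.1414 = 0.396
- SD 20 mm: 0.396 × 20 = 7.9 mm
- SD 25 mm: 0.396 × 25 = 9.9 mm
- SD 30 mm: 0.396 × 30 = 11.9 mm

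Power for a contrast D is Φ(D / (SD × √(2/100)) − 1.96). For the third case:

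| SD | D = 5 mm | D = 10 mm |
|---|---|---|
| 20 mm | Φ(1.768 − 1.96) = 42% | Φ(3.536 − 1.96) = 94% |
| 25 mm | Φ(1.414 − 1.96) = 29% | Φ(2.828 − 1.96) = 81% |
| 30 mm | Φ(1.179 − 1.96) = 22% | Φ(2.357 − 1.96) = 65% |

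These figures concern differences between loads only.

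**6. Safety.** Under section 2.4.2 the tilt is set so that gravity replaces the preload. A preload that is a larger share of body weight would be expected to need a steeper tilt, so head-down exposure probably differs by arm. Harms related to load or tilt can therefore be compared between arms. Harms that depend on neither have the same expectation in all three arms and give no contrast.

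**The case against.** **A lower-dose control is a recognised way to show an effect.** This stands. If 40% or 60% beats 20% under otherwise equal conditions, that is randomised evidence that traction load works, whether or not 20% is inert; a partly active control makes that test conservative. A reader might infer that the trial can say nothing about efficacy. The design does not support that inference. What such a result would not give is the size of the device's effect against its absence.

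**The 20% load may be justified in sources not shown.** The citations in section 2.1 or a fuller protocol may explain it. That cannot be checked, and the absence of a rationale from a condensed article is not itself the fault. But even an inactive 20% would leave a comparison of loads on one device, and the contrast would be only indirect evidence on the device.

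**Head-down harms.** A reader might infer that all harms of the head-down position cancel between arms. Section 2.4.2 points the other way, since tilt is tied to load. Adverse events are also monitored throughout (section 2.5.2), so safety can be described in each arm.

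**No inference from within-arm change is planned.** Correct: section 2.5.2 compares change between groups. The risk lies in how the aim is worded, not in a stated analysis.

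**The Discussion already asks about dose.** It does, and that is the question this design fits. It does not replace the aim in the Introduction, and the two should agree.

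**Conclusion.** The concern holds as a mismatch between the stated aim and the randomised comparison. The aim is about the device; the contrasts are about load. A higher load beating 20% would support an effect of traction load. It would not measure the total effect of the device against no device or another treatment. A null result could not separate a device that works equally at all loads from one that does not work. Harms independent of load and tilt cannot be attributed to the device by comparison.

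The conclusion rests on one inference, that the 20% arm is treated by the same procedure and schedule. It does not rest on the millimetre figures: the effects, the SD and the power are assumptions that illustrate the ambiguity, and the article gives nothing from which the real loss could be calculated. No analysis of these arms alone can close the gap, so it should be settled in the aim. It is a point that should be corrected; it does not invalidate the comparison of loads.

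**What to change.** Change the wording of the aim in the Introduction and of the conclusion the trial is permitted to draw:

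- State the aim as a comparison of VAS change between 40% and 20%, and between 60% and 20%, of body weight delivered by the same device, in line with the dose question in the Discussion.
- Delete the clause that promises to confirm a positive effect of the device.
- State that a null result is not evidence that the device is ineffective, and that improvement within an arm is not evidence of effect.
- State that device safety is described per arm, with between-arm comparison informative only for harms related to load or tilt.
- Say in one sentence that the 20% arm uses the same device and procedure, if that is so.

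The cost is a few sentences and a narrower claim. No change of arms, loads, schedule or sample size is proposed.

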## 2. Methodology

The study protocol is approved by the Medical Ethical Committee of the Affiliated Hospital of Gansu University of Chinese Medicine in March 2020 (Number: [2020]08). The trial is prospectively registered with the Chinese clinical trial registry (ChiCTR2100045118).

### 2.1. Trial design

This trial is designed as a pragmatic double-center, single-blind, and 3-arm (1:1:1 ratio) RCT to evaluate the effects of self-gravitation traction on LDH patients. The trial is being conducted in 2 hospitals in Lanzhou, China (Affiliated Hospital of Gansu University of Chinese Medicine and Gansu Provincial Hospital of Traditional Chinese Medicine). The recruited LDH patients are randomly allocated into the intervention group (traction load is 40% or 60% of their body weight) or control group (Traction weight is 20% of its body weight).^[18,20,22]^ Traction treatment procedure is completed within 6 consecutive weeks (3 times a week), 10 minutes’ traction for the first 3 weeks, then increase to 20 minutes for the next 3 weeks. See details in Figure 1.

**Figure 1. F1:**
[figure not shown]
Study flowchart.

### 2.2. Participants

#### 2.2.1.
*Eligibility*.

Adult men and women (aged 18‐50 years) who have been diagnosed with LDH using Lumbar MRI are recruited to participate in the study. These participants also need to meet the following 3 conditions: MRI result shows unilateral segmental nerve root compression; clinical LBP symptoms and sciatica have lasted for more than 3 months; volunteer to participate in the study and informed consent form is agreed and signed. All participants with any of the following conditions will be excluded from the study: Tumor, infection, or fracture-related LBP; has received surgical operations on the lumbar region; has neurological defects diseases; suffers from severe osteoporosis; suffers from mental illness, such as insomnia, depression, or anxiety; pregnant women or women whose maternity is within half a year; with severe cardiovascular disease or lung disease; with liver or kidney dysfunction; patients whose lumbar MRI/CT examination indicate lumbar disc prolapse (prolapse or upturn) or calcification.

#### 2.2.2.
*Sample size*.

Prior to launch the study officially, a pilot feasibility study (unpublished material) is conducted. Sample size calculation is based on the effective size of the pilot feasibility study. Finally, the study plan is to recruit 300 patients and distribute them at a ratio of 1:1:1, with 100 cases in each group.

#### 2.2.3.
*Recruitment and screening process*.

Orthopedist selects eligible LDH patients according to the inclusion criteria and exclusion criteria. Both outpatients and inpatients are recruited. Patients who meet the inclusion criteria are asked whether they are interested in participating in the study via face-to-face conversation or phone inquiry. Patients who agree to participate voluntarily are invited again to come to the hospitals for eligibility review. At the same time, patients are free to ask any additional questions about the study. At this point, patients who confirm to participate in sign a written informed consent, and signed participants receive an interview and complete a set of questionnaires.

### 2.3.
*Randomization and blinding*

The study adopts a central stratification and block randomization design. Patient is randomized to the study once they meet the eligibility criteria in which randomization sequence will be generated through SPSS software, version 21 (SPSS Inc. Chicago, IL). The study site of each hospital receives its randomization lists once a week from the primary study center. The randomization sequence cannot be edited and is concealed from the researcher. The aforesaid process of randomization ensures the objectivity of the researcher and eliminates bias in allocating participants groups. After the completion of blind editing, a document is prepared to record the entire process of blind editing, and the 2 copies of the blind secret will be stored in the primary study center and the application hospitals. When the study is completed, the staff who saves the blind bottom from the primary study center will do the first unblinding to get the group code, such as the experimental group or the control group. Afterward, statical data analysis will be done accordingly. Once analysis is completed, the researcher of the application hospital conducts a second unblinding and learns the 3 groups under specific interventions.

### 2.4. Interventions

#### 2.4.1.
*Monitor traction*.

Therapist will place 4 pairs of surface electrodes on the corresponding positions of the participant’s back muscles (muscle movement points) and place the electrodes parallel to the direction of the fiber (Fig. 2). Two electrodes will be separated by 2~3cm and connected to the 8-channel muscle. The surface electrical signal will be collected on the electrograph and connected to the computer analysis software to quantify the co-contraction performance of the muscle. At the same time, the electrocardiograph will be used to dynamically measure the heart rate to determine the patient’s relaxed state. Then, the therapist will use an adhesive to stick the strain gauge on the surface of the participant’s lumbar spine and connect it to a static resistance strain gauge and record the stress changes through a strain sensor (Fig. 2).

**Figure 2. F2:**
[figure not shown]
Electrode connection diagram.

#### 2.4.2.
*Phystrac mechanical traction therapy*.

Participants are in a supine position on the traction machine through adjustment, with hip and knee joints flexed at 90°, and double-fixed with a pelvic belt and ankle joint U-shaped feet (Fig. 3A). Start the weighing sensor system, apply mechanical load in advance through the axial pulling of the armpit on the horizontal plane, and will use the load cell to measure the mechanical traction. It is initially set as the preload, and on this basis, the shaft is gradually rotated to the head-down and the foot-high position, and the bodyweight will be used to complete the equivalent transformation of force (Fig. 3B). When the traction device rotates to a certain angle (the angle measuring instrument records the traction angle), the preload of the horizontal mechanical load will completely transform into its gravity. Controlled and quantified traction, continuous and repeated self-weight traction at this tilt angle.

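### The stated exclusions do not fit a head-down tilt of about 37 degrees or more: glaucoma, retinal disease and hypertension not judged severe remain eligible for the 60% arm

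*Protocol article*

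**What the plan says.** Section 2.1 sets three loads. In the intervention arms, "traction load is 40% or 60% of their body weight"; in the control arm it is 20%. Treatment is given three times a week for six weeks, with 10-minute sessions in the first three weeks and 20-minute sessions in the last three.

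Section 2.4.2 describes how the load is produced. A horizontal mechanical preload is applied to the supine patient, then "the shaft is gradually rotated to the head-down and the foot-high position", until "the preload of the horizontal mechanical load will completely transform into its gravity". Traction is held at that angle. The pelvis and ankles are fixed. The text gives neither a numerical angle nor an upper limit.

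Section 2.2.1 limits age to 18-50 and states that "All participants with any of the following conditions will be excluded from the study". Two items in the list bear on posture: "with severe cardiovascular disease or lung disease" and "has neurological defects diseases". Hypertension is not named, and there is no eye condition in the list.

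Section 2.5.1 lists the physical data taken during traction: load, displacement, skin stretch, heart rate, surface electromyography and angle. Section 2.5.2 adds adverse event monitoring over the whole study and laboratory tests at weeks 1, 6, 10 and 14. The Introduction gives the aim as to "evaluate the effectiveness and safety of the self-gravitation traction device".

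**The concern.** Load and posture are tied together in this device: a heavier assigned load means a steeper head-down tilt. The three arms therefore differ in head-down exposure as well as in traction force. Eligibility has to suit the steepest tilt, because any enrolled patient can be randomized to it.

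The list in section 2.2.1 is detailed in other respects; it goes as far as insomnia and recent childbirth. For a head-down procedure it relies on one undefined word, severe, for the circulation, and it has nothing for the eye. At stake is the safety of individual patients in the 40% and 60% arms. So is the credibility of the safety comparison, which is half of the stated aim.

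**Working it through.** The article states no tilt angle, so there is no figure to reproduce. The minimum angles follow from its own description.

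**Inputs from the article.** Loads L = 0.20, 0.40 and 0.60 of body weight W (section 2.1). The load at final tilt is carried entirely by gravity (section 2.4.2). Sessions: 3 per week for 6 weeks, 10 then 20 minutes (section 2.1). Arm size: "with 100 cases in each group" (section 2.2.2).

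**Minimum tilt.** On an incline at angle θ, the component of body weight along the table is W × sin θ. Setting this equal to L × W with the whole body pulling and no friction gives θ = arcsin(L):

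- 20%: arcsin(0.20) = 11.5 degrees
- 40%: arcsin(0.40) = 23.6 degrees
- 60%: arcsin(0.60) = 36.9 degrees

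**Why these are floors.** Two departures from the ideal case are possible, and both steepen the tilt. The article gives no value for either, so the values below are assumptions that show direction only.

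| Case | 20% | 40% | 60% |
|---|---|---|---|
| Ideal: whole body pulls, no friction | 11.5 | 23.6 | 36.9 |
| 80% of the body pulls: arcsin(L/0.8) | 14.5 | 30.0 | 48.6 |
| Friction coefficient 0.2: sin θ − 0.2 cos θ = L | 22.6 | 34.4 | 47.3 |

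Fixing the pelvis and ankles makes a pulling share below 100% plausible. Figure 3, which is not shown, could give larger angles than the floors but not smaller ones.

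**Planned exposure.** 6 × 3 = 18 sessions per participant; 9 × 10 + 9 × 20 = 270 minutes. In the 60% arm, 100 × 18 = 1,800 planned sessions. These assume full attendance. The article does not say whether the 10 or 20 minutes include the preload and rotation, so 270 minutes is the planned traction time and may overstate the time at final tilt.

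**Why posture matters for the eye.** The article gives no physiological data. As an illustration only, assume that the eye lies 25-35 cm from the heart along the body and that blood density is 1,060 kg/m³. The fluid column adds ρ × g × d × sin θ compared with lying flat:

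- 36.9 degrees: 1,060 × 9.81 × 0.25 × 0.60 = 1,560 Pa, or 11.7 mmHg; with 0.35 m, 2,184 Pa, or 16.4 mmHg
- 11.5 degrees: the same with sin θ = 0.20, 3.9 to 5.5 mmHg

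This is a simple hydrostatic rise at head level, three times as large in the 60% arm as in the 20% arm. It says nothing about systemic blood pressure, whose response to these tilts cannot be derived from the article.

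**Exclusions set against the posture.**

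- Glaucoma or retinal disease: no item covers it.
- Hypertension: covered only if the screener judges it to be severe cardiovascular disease, a term with no definition or blood pressure limit.
- Previous stroke or similar: arguably covered by the neurological item.

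**The case against.** The strongest reply is that this is a condensed article. Device contraindications, vital signs at each session and stopping values commonly sit in the full protocol. Section 2.5.1 is headed as physical data and lists device and biomechanical measurements; it does not claim to be the safety plan. A reader might infer from it that blood pressure is never taken and that a symptom-free rise in pressure would go unseen. The text does not support that. Adverse events are monitored throughout, the method is not described, and nothing says that vital signs are omitted. This part of the objection stands, so blood pressure measurement is raised below only as a conditional addition.

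A reader might also infer that every patient with uncontrolled hypertension is admitted. That goes too far as well: a screener could class marked uncontrolled hypertension as severe cardiovascular disease, and section 2.2.3 provides for an eligibility review. What remains is that the text does not require such a reading.

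Other safeguards count. Patients are at most 50 years old, rotation is gradual, heart rate is followed by electrocardiograph, and the neurological exclusion removes some patients at risk. The article gives no data on how common the relevant conditions are or on how far pressure rises, so neither the number of patients affected nor the number of harms can be stated.

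The objection does not remove the eligibility point. The exclusion list is printed in detail and can be followed as it stands, and the tilt floors follow from the stated loads and mechanism.

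**Conclusion.** The eligibility gap holds. The stated loads and gravity-only delivery imply tilts of at least 11.5, 23.6 and 36.9 degrees, planned for 10 to 20 minutes in each of 18 sessions. The printed exclusions allow patients with glaucoma, retinal disease or hypertension not judged severe to be allocated to the steepest. The angles assume only that gravity carries the whole load, as section 2.4.2 says; friction or a smaller pulling share makes them larger.

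The point should be acted on for patient safety. It does not affect the primary comparison of back pain at week 6, the randomization or the assigned loads. It does not show that the device is unsafe. Confidence is moderate, because the full protocol may already contain further limits; if so, the sponsor need only confirm them.

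**What to change.** **Main change.** Add three exclusions to section 2.2.1, applied before randomization and to all arms alike: uncontrolled hypertension, with a stated blood pressure limit; glaucoma; and retinal disease. Applying them to every arm keeps the randomized comparison intact.

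**Secondary addition, if the full protocol does not already have it.** At each session take a cuff blood pressure before tilting and again at the final tilt, with a preset value at which the table is levelled. Report the readings as a safety outcome by arm and by the tilt angle, which is already recorded. A cuff shows systemic pressure only; risk to the eye is handled by the exclusions.

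**Cost.** Eligibility becomes slightly narrower, so somewhat more patients must be screened to enrol 300; the article gives no basis for saying how many. The readings come to 2 × 18 = 36 per participant, or 36 × 300 = 10,800 in all, and take a few minutes per session. The trial is described as under way, so patients treated before the change will lack these readings. Those already enrolled with a newly listed condition need a clinical decision before further sessions. Loads, delivery, arms and primary outcome stay as they are.
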